## Abstract

**Introduction:**

Eating disorders (EDs) are a significant public health concern, yet men remain underrepresented in research and care, partly due to stigmatization. This stigmatization contributes to reduced help-seeking and recognition of ED symptoms in men. To address this, targeted interventions for healthcare professionals are needed. The iSMEsH intervention aims to sensitize general practitioners (GPs) in Germany to EDs in men, impart relevant knowledge and skills, and counter the perception of EDs as “women’s diseases”.

**Methods:**

We will evaluate the iSMEsH intervention regarding its effects on biased attitudes, knowledge, and self-efficacy among GPs. A sequential explanatory mixed-methods design (QUAN → qual) will be applied in three steps: (1) pre-implementation focus groups and a panel discussion with individuals with lived ED experience and GPs to design the intervention, (2) conduction of a randomized, wait-list controlled trial of the online training trial with GPs and medical students, and (3) post-implementation qualitative interviews with GPs. Quantitative data (step 2) will be analyzed using mixed-measures ANOVAs and contrast analyses (per-protocol) as well as corresponding 2 × 3 linear mixed models with fixed and random effects (intention-to-treat). Qualitative data from step 3 will be analyzed using thematic analysis as outlined by Braun and Clarke (2006). Ethical approval was granted by the Ruhr-University Bochum Ethics Committee (AZ 2023−1106). Participants will provide written or digital informed consent.

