### Objectives

This project aims to sensitize GPs in primary care in Germany to the occurrence and manifestation of EDs in men, to impart knowledge and specific skills, and to act against the stigmatization of EDs as “women’s diseases”. Towards that end, we will develop, disseminate, and evaluate an intervention (in terms of implementation and efficacy) adapted for Germany, based on an existing online training course, “Eating disorders in boys and men for doctors”. Although a preliminary version of the training course has already been created by our group and made openly available [19], it remains unclear who uses the course, whether it is accepted and implemented as intended, and how effective the course is as an intervention against stigmatization. Thus, the objectives of the current project are (1) to revise and optimize the existing training materials for their use in the German healthcare system, to (2) systematically record and evaluate aspects of implementation according to the “Implementation Outcomes” framework model [20] (i.e., acceptability, feasibility, appropriateness, adoption, fidelity, penetration, sustainability), and to (3) assess the effects of the intervention on reducing the identified sources of stigmatization (knowledge deficits, biased attitudes, low counselling and action competence). In this regard, we hypothesized that participation in the intervention will lead to individual increases in knowledge, decreases in stigmatizing attitudes, and increases in self-efficacy.

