### Sample size

To determine the appropriate sample size for the planned quantitative analysis (e.g., a 2x3 repeated measures ANOVA with a within-between interaction), an a priori power analysis was conducted using G*Power 3.1.9.7 software [30]. The aim was to achieve a power of.80 [31] with an alpha level of.05. A small-to-medium effect size (*f* = 0.15) as found in prior ED-related anti stigma research [15] and moderate correlation (*r* = .50) among the repeated measures were assumed, as observed in similar fields and due to practical significance considerations. The epsilon (ε) was set to 1, assuming sphericity, which is the most conservative scenario. Using these parameters, the G*Power analysis indicated that a total sample size of 74 participants is required, i.e., a minimum of 37 participants per group. Considering dropouts and cases with insufficient plausibility or quality of data, the study aims for an experimental group of approximately 50 GPs and a wait-list control group with further 50 GPs. To estimate the needs and benefits of future curricular use, the intervention will also be made accessible to approximately 50 medical students in their clinical training year. For the qualitative analyses, up to ten participants with lived experience of EDs and additional GPs for the pre-implementation focus group and panel discussion, and up to 50 GPs for the telephone-based qualitative post-implementation interviews were considered sufficient.

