### Data analysis

Qualitative data analyses will be conducted using MAXQDA [39] version 24.5.1. Quantitative data analyses will be performed using R [40] and SPSS [41].

Regarding quantitative data, we will conduct two sets of analyses. These will be per-protocol analyses and intention-to-treat analyses. For the per-protocol analyses, we will compute a 2 (intervention vs. wait-list control) x 3 (timepoint) mixed-measures ANOVA per each outcome and participant group, accounting for the two groups (intervention vs. wait-list control group) and the three time points of quantitative assessment. The intention-to-treat analyses will be conducted using a corresponding 2 x 3 mixed model, with by-participant random intercepts (and slopes, if justified by the data). We will also conduct contrast analysis for the 2 x 3 design (1 −1 −1 1 1–1) to directly test the predicted interaction pattern. The change from pre- to post-intervention will be estimated with a paired-samples t-test for any participant that completed the intervention. Quantitative implementation data will be aggregated descriptively and compared between groups.

The per-protocol analysis will use case-wise exclusions in case of missing data. In case of dropout/case exclusions, the ITT mixed model will be conducted with and without multiple imputation based on predictive mean matching functioning as a sensitivity analysis.

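### The only analysis set the protocol names for its direct hypothesis test is the per-protocol set; the Abstract and Data analysis section should be reconciled so that the directed contrast comes from the ITT model

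*Protocol article*

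**What the plan says.** The Objectives state directional hypotheses: "participation in the intervention will lead to individual increases in knowledge, decreases in stigmatizing attitudes, and increases in self-efficacy". Two sections then say how these are tested.

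- **Abstract, Methods.** "mixed-measures ANOVAs and contrast analyses (per-protocol) as well as corresponding 2 × 3 linear mixed models with fixed and random effects (intention-to-treat"). The per-protocol label follows the ANOVAs and the contrasts together. Only the mixed models stand under intention-to-treat.
- **Data analysis.** After the per-protocol ANOVA comes the ITT model: "The intention-to-treat analyses will be conducted using a corresponding 2 x 3 mixed model, with by-participant random intercepts". The next sentence is "We will also conduct contrast analysis for the 2 x 3 design", with the stated purpose "to directly test the predicted interaction pattern". No analysis set is attached to it. Further down: "The per-protocol analysis will use case-wise exclusions in case of missing data". The ITT model is to be run with and without multiple imputation.

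The Sample size section powers "a 2x3 repeated measures ANOVA with a within-between interaction", that is, the omnibus interaction. Neither the per-protocol nor the ITT analysis is called primary anywhere.

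**The concern.** The contrast is the one analysis that the protocol describes as aimed at its hypothesis. The only text that gives it a set is the Abstract, and that set is per-protocol. Case-wise exclusion makes membership depend on events after randomisation: who keeps going with a self-paced course inside a 14-day window and who returns every questionnaire.

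Loss can also differ by arm at the point where the comparison is made. Up to t2 the intervention arm has been asked to do the training, while the wait-list arm has only waited. If people who gain little tend to stop, they disappear from the trained arm but have no counterpart removed from the control arm.

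Two things are at stake: which population supports the statement that training works, and whether that choice is fixed in advance. With the set unstated in one section, stated as per-protocol in the other, and no primary analysis named, the set for the key test could be chosen after the results are known.

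**Working it through.** **1. The two sections side by side**

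| Item | Abstract | Data analysis |
|---|---|---|
| ANOVA | per-protocol | per-protocol |
| 2 × 3 mixed model | ITT | ITT |
| Contrast | per-protocol | no set named; follows the ITT sentence |
| Which set carries the conclusion | not stated | not stated |

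**2. The protocol's own sample size.** Inputs from the Sample size section: f = .15, r = .50, ε = 1, α = .05, two arms, three time points. Noncentrality λ = f² × N × 3 / (1 − r), with 2 and 2(N − 2) degrees of freedom.
- N = 72: power .795.
- N = 74: λ = .0225 × 74 × 3 / .5 = 9.99, power .806.
- N = 100: λ = 13.5, power .914.

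The stated 74 reproduces. No figure in the protocol is wrong on this point.

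**3. What f = .15 means if the arms differ only at t2 (assumed pattern).** A t2 difference of d SD gives interaction effects of d/6, d/3 and d/6 in absolute size in each arm. Their mean square is d²/18. So d = .15 × √18 = .636 SD.

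**4. Illustrative selection shift.** If retention depends on a latent normal variable that correlates ρ with the gain, the mean gain among those retained is too high by ρ × φ(z)/p, in SD of change. At r = .50 the SD of change is √(2 × (1 − .50)) = 1 outcome SD. Take p = .74, from 74 needed out of about 100 sought. Then φ(z)/p = .324/.74 = .438.

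| ρ (assumed) | Shift (SD) | Share of .636 |
|---|---|---|
| .1 | .044 | 7% |
| .2 | .088 | 14% |
| .3 | .131 | 21% |
| .4 | .175 | 28% |

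Neither p nor ρ is given in the protocol as used here. The 26 extra GPs cover dropouts and also implausible or poor-quality data, so .74 is not a stated completion rate.

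**5. Power of the contrast to be moved.** The arm difference in change from t1 to t2 has weights (−1, 1, 0). The t2-only pattern corresponds to (−1, 2, −1). The share of λ captured is (1 + 2)² / (2 × 6) = .75.
- N = 74: λ = 7.49, power about .77 to .78. Direct check: .636 / √(2/37) = 2.74, and 2.74² is about 7.5.
- N = 100: λ = 10.1, power about .88 to .89.

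The ranges reflect change-score or pooled error degrees of freedom. The omnibus test has .81 and .91. All these figures assume complete data.

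**The case against.** **The contrast may cover both sets.** The Data analysis section is the operative text. It announces two sets of analyses, describes both, and then adds the contrast directly after the ITT model without restricting it. A reader might infer from the Abstract that the contrast is per-protocol only; the documents do not settle that. This stands, and it is why the point is a discrepancy to reconcile and not a proven restriction.

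**ITT is not left without a signed result.** A reader might infer that the randomised set gets only a non-directional F test. That does not follow. With t1 as reference, the arm-by-t2 coefficient of the 2 × 3 mixed model is the difference in change from t1 to t2, with a standard error. What is missing is the statement that this coefficient is the confirmatory estimate.

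**Power is no reason for the change.** A reader might infer that a one-degree-of-freedom contrast must beat the omnibus test. That is so only if its weights match the true pattern (.88 at N = 74 for a perfect match). The t1-to-t2 contrast is slightly weaker than the omnibus test under a t2-only difference.

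**ITT may not remove the selection shift.** The post-training assessment follows the training, and the Participant timeline does not say that non-completers are assessed at t2. If those values are missing and depend on the unobserved gain, neither the mixed model nor predictive mean matching corrects the bias. This also stands. ITT still uses randomised participants whom case-wise exclusion would drop, for example those who miss only t3.

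**No section says that efficacy claims will rest on the per-protocol result.** True, but none says that they will rest on ITT either.

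**Conclusion.** The point holds as a discrepancy that affects the choice of analysis population. The Abstract puts the designated hypothesis test in the per-protocol set, the Data analysis section leaves its set open, and neither analysis is declared to carry the conclusion. If the Abstract is followed, the efficacy test rests on participants selected after randomisation, while the corresponding ITT coefficient exists but has no confirmatory role.

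The amount of bias is unknown. The .04 to .18 SD range is only an illustration under assumed retention of 74% and assumed correlations of .1 to .4, and it is not the amount that ITT would recover. The case rests on keeping the randomised comparison and on fixing the set in advance, not on power and not on an absence of direction in the ITT model.

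**What to change.** Align the Abstract and the Data analysis section so that both say the following:

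- The directed contrast is the arm difference in change from t1 to t2, per outcome, with a 95% CI. It is estimated from the planned ITT mixed model on all randomised participants. At t3 the wait-list arm has been trained as well, so this interval is the one that compares trained with untrained participants.
- The multiple-imputation version of that model is the sensitivity analysis.
- The efficacy statement rests on this estimate, and the per-protocol contrast is supportive.

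The weights printed in the Data analysis section come without a cell order. That is a separate matter, but writing the contrast out in words at the same time would avoid doubt about what is estimated.

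The cost is two sentences and one contrast on a model already planned, with no new data or participants. The downsides are that the ITT estimate may be less favourable than the per-protocol one, and that this contrast has slightly less power than the omnibus test under a t2-only difference (about .77 against .81 at N = 74).

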**Discussion:**

The intervention seeks to reduce stigma against men with EDs in primary care by improving GPs’ and medical students’ knowledge, attitudes, and self-efficacy. Strengths include the comprehensive mixed-methods approach and involvement of people with lived experience. Limitations are reliance on self-report and short-/intermediate-term outcomes. If effective, iSMEsH may offer a foundation for future stigma-reduction strategies in healthcare.

## Introduction

### Background and rationale

Eating disorders (EDs) are a growing public health concern [1]. Their most common forms include Binge-eating disorder (uncontrollable binge eating episodes without compensatory behaviors), Bulimia nervosa (binge eating episodes followed by compensatory behaviors), Anorexia nervosa (restrictive eating leading to underweight), and other as well as subthreshold forms that do not eet the exact diagnostic criteria of the previously mentioned categories. People with EDs often have considerable health impairments and a significantly increased mortality risk compared to the general population [2]. Due to the frequent occurrence in adolescence, long duration of illness and repeated inpatient stays, the treatment costs are substantial [3].

Although women constitute the majority of ED cases across age groups, prevalence estimates suggest that men could account for every fourth case [4]. Men, however, remain underrepresented in ED research and care, for example, with one man with Anorexia nervosa or Bulimia nervosa for every 10–20 women in specialized treatment facilities [5,6]. One of the many probable reasons for men’s underrepresentation may be the so-called “double stigmatization” [7]: Men conceal having an ED not only because they are ashamed of having a mental disorder itself, but also because having an ED, which is broadly considered a “women’s disease”, conflicts with traditional gender roles and masculine identity norms. Internalizing such stereotypes (in the sense of self-stigmatization) makes recognizing and disclosing ED symptoms in medical and therapeutic contexts unlikely, and has been shown to reduce help-seeking intentions [8,9].

Men’s self-imposed stigmatization makes it essential for physicians to regularly ask about EDs in men, address them, if suspected, and refer men to appropriate treatment. At the same time, the stereotype of EDs as a “women’s disease” also shapes the views and behaviors of medical professionals [10]. A systematic review by our group of the experiences of men with EDs evidenced that symptoms often remain undetected, complaints are not being taken seriously, and the willingness to provide care by healthcare professionals is low [11]. Treatment access is further complicated by the fact that ED symptoms and body ideals often differ between men and women (e.g., striving for high muscle mass vs. a slim body shape) [12]. The question of how stereotypes and stigmatization in healthcare professionals and medical care for men with EDs can be combated remains.

Previous studies suggest that combined approaches of providing information and contact with those affected pose an effective anti-stigma strategy in working with healthcare professionals, like, for example, in the Canadian Opening Minds Anti-Stigma Initiative [13,14]. Similar approaches have been explored in the specific context of EDs [15]. Based on research into illness narratives, Bartel and Baker [16] developed a training course as an online intervention for UK general practitioners (GPs), which combined perspectives from men with EDs and educational materials via animated videos and art-based interventions. In Germany, there are currently campaigns aimed at informing men with EDs [17], but there are no interventions that explicitly address GPs, despite their key role as gatekeepers in the German healthcare system [18]. Thus, there is a continuing need to act against the stigmatization of men with EDs among GPs in Germany.

### Objectives

This project aims to sensitize GPs in primary care in Germany to the occurrence and manifestation of EDs in men, to impart knowledge and specific skills, and to act against the stigmatization of EDs as “women’s diseases”. Towards that end, we will develop, disseminate, and evaluate an intervention (in terms of implementation and efficacy) adapted for Germany, based on an existing online training course, “Eating disorders in boys and men for doctors”. Although a preliminary version of the training course has already been created by our group and made openly available [19], it remains unclear who uses the course, whether it is accepted and implemented as intended, and how effective the course is as an intervention against stigmatization. Thus, the objectives of the current project are (1) to revise and optimize the existing training materials for their use in the German healthcare system, to (2) systematically record and evaluate aspects of implementation according to the “Implementation Outcomes” framework model [20] (i.e., acceptability, feasibility, appropriateness, adoption, fidelity, penetration, sustainability), and to (3) assess the effects of the intervention on reducing the identified sources of stigmatization (knowledge deficits, biased attitudes, low counselling and action competence). In this regard, we hypothesized that participation in the intervention will lead to individual increases in knowledge, decreases in stigmatizing attitudes, and increases in self-efficacy.

### Trial design

This study adopts a sequential exploratory mixed-methods design (QUAN → qual) guided by pragmatism principles (see Fig 1) [21]: In a pre-implementation stage (1), we will use both qualitative and quantitative data from a focus group, panel discussion, and rating procedure with both individuals with lived experience of EDs and GPs to guide the editing and adaptation of the intervention. In the implementation stage (2), we will deliver the online training in a randomized, wait-list controlled multiple group design to GPs and medical students in their clinical training year (“Praktisches Jahr”, last year of medical school), assessing quantitative endpoints of implementation and efficacy (‘QUAN’) before and after the participation. In a final post-implementation stage (3), we will then conduct telephone-based qualitative interviews (‘qual’) with GPs who participated in the online training assessing further implementation outcomes.

**Fig 1 pone.0333997.g001:**
[figure not shown]
Visual model depicting the mixed-methods trial design. GP = General practitioner.

## Materials and methods

### Study setting and participant recruitment

Study participants will be recruited nationwide, targeting individuals with lived experience of EDs, GPs, and medical students. Recruitment will be conducted through offline and online methods, including leaflets, personal recommendations and mass emailings. We will perform extensive web-scraping of contact registers of medical professional organizations and apply for access to the federal register of physicians for a nation-wide probability sample of GPs. Medical students in their clinical training year will be recruited through local university networks and mass emailing via clinical training year coordinators at medical faculties across all German universities.

Individuals with lived experience will be rewarded 100 € for participating in the focus group, and 75 € for each attended advisory board meeting (for further details, see section on Patient and Public Involvement). GPs participating in the online training will receive 25 € reimbursement upon completion as well as 1 continuing medical education (CME) credit point, and another 50 € for participating in the telephone-based qualitative interview. Medical students will be eligible to register for a prize draw to win online vouchers worth 375 € in total. All participants will receive a certificate upon successful completion of the online training.

### Eligibility criteria

Focus group participants with lived experience of an ED must (i) identify as male, (ii) be aged 18 years or older, (iii) able and willing to provide written informed consent, and (iv) endorse having received a current or past ED diagnosis. Participants with lived experience of an ED will be excluded if, during the preliminary meeting, they exhibit significant distress related to their ED or to discussing it. The focus group will further include GPs, who are eligible if they are (i) of legal age and capacity and (ii) regularly treat men in their healthcare institution.

To be included in the online training intervention, participants (i) must be aged 18 years or older, (ii) work in the German healthcare system as a GP, or study medicine at a German university in their clinical training year (“Praktisches Jahr”), (iii) are involved in the medical treatment of men in their current position, and (iv) be able and willing to provide written informed consent. Individuals not meeting these criteria will be excluded from the study.

### Intervention

Eligible participants will be randomized to the intervention (i.e., immediate access to the 14-day self-paced online training period) or to a wait-list control group (i.e., 14-day delay before online training access) following a 1:1 ratio using a random number generation procedure implemented in Microsoft Excel. Participants will be blinded as per the different conditions. The intervention will consist of an on-demand online training which will be implemented in a Moodle learning management system to ensure better integration into the everyday work of clinicians through easy accessibility and self-paced learning. Such formats are common in the field [22] and follow recommendations for engaging online trainings [23,24]. For reasons of compatibility with everyday working life, we also deliberately opted for short, separate modules after carefully weighing up the advantages and disadvantages. The six modules are presented as learning videos with presentation slides, demonstrational dialogues, reflexive exercises and supporting downloadable in-depth resources, and should be completed online in 5–10 minutes each (corresponding to a total duration of 45–50 minutes), followed by interactive questions, ratings and quizzes. The module structure and corresponding contents are summarized in Table 1.

**Table 1 pone.0333997.t001:** iSMEsH Online Training Intervention Modules and Content.

Module #	Title	Content
1	Introduction to Eating Disorders	• Diagnostic criteria, clinical impressions and epidemiology of EDs in Boys and Men • Etiological Concepts • Promoting sensitivity to diversity • Implications of stigmatization as “second illness”
2	Symptoms and Diagnostics	• Clinical signs for suspected EDs on the psychological, social and physical level • Guiding questions for psychological and physical examination • Standardized diagnostic instruments (questionnaires, interviews) • Basic principles of somatic co-treatment • (Compulsive) hospital referral and stepped care
3	Communication Skills	• Recommendations for inclusive and non-discriminatory communication • Directly addressing stigma with patients • Basic principles and concepts of Motivational Interviewing • Perspective-taking exercise
4	Muscle Dysmorphia	• Diagnostic criteria, clinical impression and epidemiology of muscle dysmorphia as a subtype of body dysmorphic disorder • Role of physical exercise and substance abuse (e.g., anabolic steroids) • Masculinity ideals and male body image • Reflexive exercise on own internalized gender roles and masculinity concepts
5	Therapeutical, Social and Other Support Services	• Barriers to care for boys and men • Role of self- and public stigmatization and structural discrimination • Recommendations for adequate care • Introduction to medical, psychotherapeutic, social and other support services
6	Role and Support of Caregivers	• Inviting, inclusive and non-discriminatory communication with caregivers • Role of caregivers in the treatment process • Active support for caregivers

iSMEsH = Intervention Against the Stigmatization of Men with Eating Disorder in Primary Care; ED = Eating disorder.

The contents of the intervention are based on a social-cognitive and sociological understanding of ED-related stigma as a multi-facetted construct: (a) knowledge deficits (i.e., stereotypes), (b) biased attitudes (i.e., prejudices), and (c) behaviors (i.e., discrimination) [13]. Based on this understanding of stigma, the contents of the planned intervention thus combines demonstrably effective measures to reduce stigma [15], namely (a) thorough information to reduce knowledge deficits, (b) contact with the perspective of men with lived experience to reduce prejudice via patient narratives and case examples, and (c) the teaching of practical skills (e.g., via exemplary dialogues, hands-on recommendations and wordings for assessment and counseling) and the provision of resources to develop non-discriminatory counseling and treatment skills. The intervention will be established with extensive patient and public involvement, closely building up on the needs and narratives of up to ten men with ED experience and the recommendations of two GPs from a focus group prior to dissemination.

